#### Focus groups of veterans

Veterans in CBSST-Peer and SST-Peer conditions who indicated they would be willing to participate in a focus group at the time of consent will be invited to a face-to-face or virtual focus group once they have completed the study. Open-ended questions will ask about helpfulness and will focus on the utility of learning about errors in thinking and social skills. Participants of the CBSST-Peer group will be asked about whether there was any added impact of having the cognitive training over and above social skill training. There will also be questions asked about the benefit of having peer specialists run the groups (vs. non-peer providers). Saturation is generally reached with two groups of each “type” of participant [31]. To achieve saturation, four focus groups will be conducted (2 for SST-Peer; 2 for CBSST-Peer). Each group will last 60 min and include up to 8 participants, consistent with the established standards for successful focus groups [32]. Veterans will be randomly selected and consented for participation and audio taping and will be compensated $25 for their time. Each focus group will be audio-taped using a VA-approved recorder and transcribed verbatim.

#### Interviews of peer specialists and administrators

We will interview all participating peer specialists who delivered at least 10 sessions (anticipated to be *n* = 5) and all key mental health administrators (*n* = 4). These numbers will allow for saturation given they represent the full universe of peer specialists and key administrators from the study. These individuals will be asked about implementation barriers and facilitators. Specific probes will be drawn from the Consolidated Framework for Implementation Research (CFIR) [33]. The CFIR was chosen as it combines theories from across implementation science and covers five key domains: intervention characteristics, inner context (host organization), outer settings (environment-at-large), individuals involved, and the implementation process. Each domain is further divided into unique subdomains that provide areas to explore, as applied to SST- and CBSST-Peer—in other words, a defined list of specific barriers and facilitators shown to be important to implementation.

### Trial oversight

The study team will meet weekly to review the recruitment and retention progress. Our funder, the VA’s Health Services Research and Development (HSR&D) service, did not require additional trial oversight beyond what is already required, which is annual reporting to HSR&D and to the requisite IRB.

### Peer specialists

Peer specialists will be VA employees who are hired using the VA’s national guidelines for peer specialists, which specify the qualifying mental health conditions. These guidelines state that “a serious mental illness like schizophrenia, bipolar disorder, major depression, depression and anxiety disorders, post-traumatic stress disorder (PTSD), and substance use disorders qualify” [34]. Peer specialists will receive a full-day training in CBSST-Peer from CBSST experts. Part of the training involves developing their own examples to demonstrate the skills to be taught. For SST-Peer, each peer specialist must complete a 4-h online training course and pass the evaluation test. Then, an SST Master Trainer will hold a full-day training. After that, using audio tapes, the peer specialists will be evaluated and mentored over 6 months on their fidelity to the SST model. Peer specialists will receive weekly supervision on both interventions.

### CBSST-Peer condition

Peer specialists will co-lead a series of CBSST-Peer classes in two 10-class “modules”—the CBSST Cognitive Skills Module and the CBSST Social Skills Module—for a total of 20 weekly 60-min classes. These modules have been extensively tested and were used in the pilot. Veterans will continue to receive all other standard care, medication, and other services, regardless of group assignment, throughout the study. Standard CBSST integrates CBT and SST techniques and neurocognitive compensatory aids [35]. The treatment manual includes a patient workbook that describes the skills and includes homework assignments. Thought-challenging techniques are combined with role-play practice of communication skills. Compared to traditional CBT, much less training is required to become proficient at these thought-challenging skills. This is a standardized curriculum that can be delivered by most mental health providers, and the above adaptations make it especially appropriate for peer specialists. Cognitive interventions are used to address symptoms and challenge defeatist attitudes that interfere with real-world skills execution, including expectancies (“It won’t be fun”), self-efficacy attitudes (“I always fail”), and anomalous attitudes (“Spirits will harm me”) that interfere with skill performance, despite intact skill capacity. By challenging defeatist attitudes, patients are more likely to engage in functional behaviors and use the skills they have. To simplify learning and help patients remember and use cognitive techniques in everyday life, mnemonic aids are provided (e.g., laminated cards describing skills). For example, for thought challenging, we use an acronym, “The 3C’s: Catch it, Check it, Change it.” The “it” is a thought.

We have adapted standard CBSST to be delivered by peer specialists, capitalizing on the unique lived experiences of peer specialists to strengthen CBSST in several ways. First, peer specialists will provide personal examples of how they used the skills they are teaching to improve their own recovery. This makes the skills more tangible and less abstract, compensating for cognitive problems, and improving understanding of how specific skills can be used to achieve personal recovery goals. Peer specialists develop their examples as the part of the training, where they are given feedback about how to appropriately communicate the desired content. Second, engagement and retention of veterans with SMI in evidence-based psychosocial interventions is a persistent challenge and peer specialists can help overcome this barrier by instilling hope (“if they can use these skills to recover, I can too”). Hope and empowerment may improve motivation for treatment to overcome engagement and retention barriers. Third, more sessions have been added to allow for more practice time.

#### Recovery goal-setting session

Setting functional recovery goals is a key component of the CBSST program. During the first group session, veterans identify a long-term, personally meaningful recovery goal related to living, learning, working, or socializing. Together with the peer specialist, they divide their goal into short-term steps that can be accomplished each week. The skills training in the modules are then used to facilitate working on these steps. The goal-setting session is reviewed at the beginning of each module to review goal progress and develop new steps.

### Social skills training-peer condition

These groups will run according to the Bellack et al. model [30] used in VA’s national dissemination of SST. Peer specialists will receive the standard training that licensed independent practitioners (LIP) receive (peer specialists also are trained in SST, but current VA policy states they cannot deliver SST unless paired with an LIP). Similar to CBSST, these groups will use behavioral rehearsal role-play to improve communication and interaction skills. However, an important difference is that these groups will not include any cognitive training. There is flexibility in how long these groups run; however, to make the groups equivalent, we will make these groups last the same 20-week period.

### Analyses

#### Statistical analyses

Primary analyses will use hierarchical linear models (HLMs) for continuous variables. The HLMs will include random person-level intercepts and random time slopes. Possible random effects for cohort and peer specialist heterogeneity will be explored. Analyses will include all available data with maximum likelihood estimation, which is preferred over multiple imputations. All tests will be two-sided with alpha = 0.05.

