**Methods:**

This study is a randomized, hybrid 1, research assistant-blinded, superiority trial. A total of 252 veterans with SMI will be recruited and randomized to one of three arms: CBSST-Peer vs. SST-Peer vs. treatment as usual. Participants randomized to CBSST-Peer or SST-Peer will participate in a 20-week group-based intervention that meets weekly for a 60-min class. All participants will complete 4 study assessments at baseline, 10 weeks, 20 weeks, and 32 weeks. A multidimensional battery of functional outcomes will be used with the Independent Living Skills Survey (ILSS) as the primary outcome measure. Post-study completion, veterans who participated in the CBSST-Peer or SST-Peer arms will randomly be invited to participate in focus groups, and peer specialists will complete interviews to further assess the effectiveness of each intervention.

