##### Aim 1: Power

Power estimations are from the Stata power simulation package powersim. Data from previous trials and other SST trials were used to obtain effect size estimates to guide simulations of expected ILSS scores in CBSST-Peer, SST-Peer, and TAU. We first estimated power for statistically significant treatment main effect across various sample sizes, assuming 80% retention through the final 3-month follow-up assessment and *α* = 0.05 (two-tailed). For the treatment effects (CBSST-Peer vs. TAU; CBSST-Peer vs. SST-Peer; SST-Peer vs. TAU), we estimate small to medium effect sizes (*d* = 0.35) for ILSS over 20 weeks of treatment and 3-month follow-up. For *d* = 0.35 and retention of 80%, estimated power is 0.94 for *N* = 84 per treatment type and 0.83 for *N* = 67 per treatment type. This is consistent with previous trials of CBSST and SST in which CBSST produced the largest effect sizes (*d* = 0.649) and SST produced improvements, but lower effect sizes [36]. For each group × time interaction effect (comparing each group to each other over time), we project a medium (*d* =0.45) treatment type × time effect size, based on the assumption that CBSST-Peer will produce the largest increase in outcomes per month, based on our prior and other SST trials. For this effect size and our projected enrollment, power for the treatment type x time interaction is sufficient (> 0.80).

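### Two arms are treated in classes, but the primary model leaves the cohort effect optional and the power text makes no mention of clustering

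*Protocol article*

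**What the plan says.** The Abstract (Methods) states that veterans in either active arm "will participate in a 20-week group-based intervention that meets weekly for a 60-min class". The sections on the two conditions describe role-play practice within these groups, and in CBSST-Peer co-leading by peer specialists. TAU veterans attend no study class.

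Under Statistical analyses, the random effects that the plan commits to are a person-level intercept and a time slope. The Aim 1 effectiveness section describes the primary model again with the same two terms. Group-level variation gets one sentence: "Possible random effects for cohort and peer specialist heterogeneity will be explored". No rule for keeping or dropping these effects is given.

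Under Aim 1: Power, the inputs listed are the effect size ("we estimate small to medium effect sizes (*d* = 0.35) for ILSS over 20 weeks of treatment and 3-month follow-up"), 80% retention, two-sided alpha 0.05 and the number per arm. The result is that "estimated power is 0.94 for *N* = 84 per treatment type and 0.83 for *N* = 67 per treatment type". Class size, ICC and clustering are not mentioned.

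**The concern.** This is an individually randomised trial with partial nesting: veterans in two arms share a class and its leaders, and veterans in the third do not. Shared treatment can make outcomes within a class alike. A model with person-level terms only treats veterans as independent and then understates the variance of an arm mean. Both sides of CBSST-Peer vs SST-Peer are affected; only one side of a contrast with TAU is.

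The primary hypothesis includes CBSST-Peer vs SST-Peer, so the most exposed contrast is a primary one. At stake are its type I error and the adequacy of 84 veterans per arm. Making the term optional is weak protection, because a variance component estimated from few classes is hard to detect even when it is real.

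**Working it through.** **Inputs from the protocol.** 252 veterans in three arms, so 84 per arm; d = 0.35; two-sided alpha 0.05; 80% retention; stated power 0.94 at 84 per arm and 0.83 at 67 per arm.

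**Inputs assumed, because the protocol does not give them.** Class size m = 8; ICC = 0.02, 0.05 or 0.10, on the person-level mean of the post-baseline scores.

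**The plan's own power.** A single-occasion comparison without loss has noncentrality 0.35 × √(84/2) = 2.268, so power is Φ(2.268 − 1.960) = 0.62; at 67 per arm it is 0.53. The plan uses repeated measures, which raises power. With three post-baseline visits, baseline adjustment and an assumed within-person correlation of 0.5, power is 0.94 at 84 but 0.88 at 67. Scaling 0.94 from 84 down to 67 also gives 0.88, and scaling 0.83 from 67 up to 84 gives 0.90, so no single variance factor yields both stated figures. The correlation and variance inputs of the simulation are not shown, so the stated figures can be neither confirmed nor called wrong. Below, 0.94 is taken at face value as a figure without clustering; that is an assumption.

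**Design effect.** In an arm treated in classes, DE = 1 + (m − 1) × ICC; in TAU it is 1. The variance of a contrast is multiplied by V = DE for CBSST-Peer vs SST-Peer and by V = (1 + DE)/2 for an active arm vs TAU.

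**Type I error if the term is omitted:** 2 × [1 − Φ(1.960/√V)].

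**Power if clustering is modelled:** Φ(3.515/√V − 1.960), where 3.515 = 1.960 + 1.555 is the noncentrality that gives power 0.94.

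| ICC | DE | V, CBSST vs SST | V, vs TAU | Type I, CBSST vs SST | Type I, vs TAU | Power, CBSST vs SST | Power, vs TAU |
|---|---|---|---|---|---|---|---|
| 0.02 | 1.14 | 1.14 | 1.070 | 0.066 | 0.058 | 0.909 | 0.925 |
| 0.05 | 1.35 | 1.35 | 1.175 | 0.092 | 0.071 | 0.857 | 0.900 |
| 0.10 | 1.70 | 1.70 | 1.350 | 0.133 | 0.092 | 0.769 | 0.857 |

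Example: at ICC 0.05, √1.35 = 1.162. Then 1.960/1.162 = 1.687, with two-sided tail area 0.092; and 3.515/1.162 − 1.960 = 1.065, with Φ = 0.857.

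These are normal approximations. A correction for few classes would lower the power a little further.

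**If the term is explored and then kept or dropped.** The plan gives no rule, so one was assumed: keep the class effect if an F-test has p < 0.05. Simulation of CBSST-Peer vs SST-Peer used 10 classes of 8 per arm, person-level means and 40,000 replicates:

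| ICC | Term kept | Type I, never modelled | Type I, explored | Type I, always modelled |
|---|---|---|---|---|
| 0.02 | 12% | 0.065 | 0.058 | 0.049 |
| 0.05 | 29% | 0.092 | 0.071 | 0.049 |
| 0.10 | 59% | 0.137 | 0.075 | 0.053 |

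Selection by AIC gives 0.060, 0.074 and 0.079 for the explored column. A rerun with another seed agreed with the F-test table to within 0.006. Exploration reduces the inflation but does not remove it; always modelling the effect does.

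**The case against.** A reader might infer that the standard errors of the active arms will be too small. The document does not establish this. It takes both a positive ICC and omission of the term. The plan names cohort and peer specialist as levels to examine, so clustering was recognised, and cohort may well mean the class. If the term is kept, the standard errors account for it and the only cost is power. That stands.

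A reader might also infer that the power calculation ignored clustering. Only the text is silent: the figures come from a simulation whose inputs are not shown.

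The number of classes, closed membership over the 20 weeks and the recording of class membership are not stated, so none can be treated as fact. The rule that admits terms according to model fit is written for covariates, not random effects. A retention rule and a degrees-of-freedom method are details that an article may leave to an analysis plan, which is not shown here.

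The size is modest at low ICC: at 0.02 the type I error is at most 0.066 and power stays at about 0.91 or more. Contrasts with TAU carry half the added variance. Peer specialists are supervised in both interventions, so their effects may be crossed with arm and partly cancel in CBSST-Peer vs SST-Peer.

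What survives is narrower. The article is not silent on clustering: it specifies the primary random effects twice and words the group-level ones as optional.

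**Conclusion.** The point holds as a conditional one. The primary model should not leave the class or cohort effect to exploration in a design where two of three arms are treated in classes. With 8 per class and ICC 0.02 to 0.10, omission would put type I error at 0.066 to 0.133 for CBSST-Peer vs SST-Peer and 0.058 to 0.092 vs TAU. Exploration under the assumed rules leaves it at about 0.06 to 0.08 for the former contrast.

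If the stated 0.94 has no clustering allowance, power with clustering modelled is 0.91 to 0.77 for CBSST-Peer vs SST-Peer and 0.925 to 0.86 vs TAU. It drops below 0.80 only for CBSST-Peer vs SST-Peer at the highest ICC. All of these sizes rest on assumed class sizes and ICCs.

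**What to change.** In the primary model, prespecify a random effect for class or cohort in CBSST-Peer and SST-Peer, with each TAU veteran as a singleton (a partially nested model). Keep it whatever its significance or its effect on model fit.

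Fit by restricted maximum likelihood with Kenward-Roger or Satterthwaite degrees of freedom. The plan specifies maximum likelihood and Kenward-Roger is built on REML, so the estimation sentence must change too. REML still uses all available data under missing at random.

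If classes enrol on a rolling basis, a simple nested effect does not fit; use a multiple-membership or entry-cohort version. Treat peer specialist effects as a sensitivity analysis, allowing for crossing with arm.

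Restate power with the expected class size and an ICC range such as 0.02 to 0.10, and say whether the existing simulation included clustering.

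The cost is a change of analysis wording, a somewhat less favourable power figure, and the need to record each veteran's class. No added participants or visits are needed for the analysis change.

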### Participant eligibility

The following inclusion criteria, selected to increase generalizability, will be used: (1) age 18 and older; (2) primary diagnosis of SMI documented in the medical record (schizophrenia, schizoaffective disorder, bipolar disorder with psychotic features, major depression with psychotic features, delusional disorder, schizophreniform disorder, another specified schizophrenia spectrum, and other psychotic disorders); and (3) fluency in English. The exclusion criteria are as follows: (1) medication changes in the prior month; (2) significant current or recent (within the past year) CBSST or SST; (3) level of care at baseline that interferes with outpatient participation; (4) current hospitalization for psychiatric, substance use, or physical illness; (5) inability to pass a screening for cognitive impairment [18] during informed consent process; (6) inability to pass the 10-item T/F quiz about the details of the study informed consent, (7) current pregnancy; and (8) current incarceration.

Veterans will continue to receive ongoing care with their current providers, which for this population typically includes medication management, case management, and occasional psychotherapy targeting disorder-specific symptoms. This treatment will continue independent of the study, and no one involved in the study will make decisions regarding pharmacotherapy or other behavioral health treatments for the veteran. Participants will be withdrawn if they demonstrate a repeated pattern of non-participation and indicate they are no longer interested or do not respond.

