#### Drop-out/retention

Based on our prior studies, we expect a dropout rate of 20% or less through the 32-week study period. Our prior trials with longer protocols had 86% retention after 18 months and 82% retention after 15 months. Retention will be aided by the provision of transportation. Assessments will be attempted with all participants, regardless of study retention. All analyses will follow an intention-to-treat approach that includes all participants randomized to a study group.

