##### Aim 1: Effectiveness analysis and hypothesis

Analyses will test our hypothesis that veterans in CBSST-Peer will have superior functioning, recovery, attitude, and skill knowledge outcomes during treatment and follow-up relative to veterans in SST-Peer or TAU, and further that veterans in SST-Peer will have superior outcomes relative to TAU. Secondarily, we will apply all analyses to the symptom measures and explore the impact of gender and racial/ethnicity status where sample size allows. Analyses will follow the same pattern for all the above assessments. We will examine scores obtained at weeks 10 (mid-intervention), 20 (end-of-intervention), and 32 (post-intervention follow-up) as the outcome in HLM, with treatment condition included as a time-invariant covariate, and random intercepts for person and random slopes for time. All available data will be included in accordance with maximum-likelihood estimation procedures with data assumed missing-at-random, an assumption that will be tested with baseline clinical and demographic data. Preliminary analyses will examine potential baseline differences between the three conditions. Relevant covariates including treatment attendance, baseline symptom severity (via BPRS, CAINS), care services, and medications received (standard variables from the PSR toolkit), and demographic variables will be tested and included in the overall model according to model fit. The primary analysis will compare CBSST Peer to SST-Peer and TAU with independent contrasts in the HLM model of all post-baseline time points, to directly test the primary hypothesis that CBSST-Peer has superior outcomes than the other treatments (we will also compare SST-Peer to TAU). As compared to the group by time interaction, this test typically has greater power and is less susceptible to sample-specific artifacts (e.g., regression to the mean, variability in change over time). However, we also wish to examine the degree of change in outcomes over time in CBSST-Peer vs SST-Peer vs TAU. Thus, we will conduct additional analyses to test the treatment condition × time interaction, to examine the question of whether CBSST-Peer has greater improvement in outcomes over time than the other treatments.

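### Attendance can enter the analysis only as a fit-selected outcome covariate; it should be an auxiliary variable for missing scores in a supportive analysis, with the maximum-likelihood HLM kept as primary

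*Protocol article*

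**What the plan says.** Under Statistical analyses, the protocol article sets the missing-data method: "Analyses will include all available data with maximum likelihood estimation, which is preferred over multiple imputations". Under Aim 1: Effectiveness analysis and hypothesis, the outcome in the hierarchical linear model (HLM) is the score at weeks 10, 20 and 32, with "data assumed missing-at-random, an assumption that will be tested with baseline clinical and demographic data". The same section gives attendance its one role. It lists "Relevant covariates including treatment attendance, baseline symptom severity (via BPRS, CAINS), care services, and medications received", together with demographic variables, and says these "will be tested and included in the overall model according to model fit".

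Three other statements bear on this:

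- Participant eligibility: "Participants will be withdrawn if they demonstrate a repeated pattern of non-participation and indicate they are no longer interested or do not respond".
- Drop-out/retention: "we expect a dropout rate of 20% or less through the 32-week study period". The team will also try to assess everyone, including those who leave.
- Drop-out/retention: all analyses are by intention to treat, with every randomised participant included.

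**The concern.** Maximum likelihood and multiple imputation agree, in large samples, when they use the same variables under compatible models. They can differ when a variable predicts both missingness and outcome but does not belong in the outcome model. Class attendance is a natural candidate. The article regards it as relevant to outcome, and the withdrawal rule connects it, conditionally, with leaving the study. It is measured after randomisation and is undefined under TAU.

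The HLM described leaves two options. If attendance enters the outcome model because fit favours it, the arm coefficient is no longer the intention-to-treat effect. If it stays out, it cannot inform the missing scores. The check of the missing-at-random assumption uses baseline data only, so it would not show drop-out that depends on attendance. A veteran lost before week 10 has no outcome row and adds nothing to the comparison. At stake are the two contrasts with TAU, which answer whether peer-led classes beat usual care.

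**Working it through.** **Figures in the article.** Drop-out is 20% or less; d = 0.35 for each pairwise contrast; power is 0.94 for 84 per arm and 0.83 for 67 per arm at 80% retention. The article gives no figure for this bias. The stated power came from a simulation whose within-person correlation is not reported, and no simple formula tried returned both values. For example, a baseline-adjusted mean of three visits at correlation 0.5 gives 0.94 and 0.88 without loss, and 0.88 and 0.80 with 20% loss. The stated power is used here only for scale: 0.94 at d = 0.35 implies a standard error of 0.35/(1.960 + 1.555) = 0.10 SD.

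**Assumed inputs (not in the article).**

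- Within-person correlation 0.6.
- Attendance averages 12 of 20 classes, SD 4.
- Outcome rises by g = 0, 0.15 or 0.30 SD per SD of attendance.
- Log-odds of drop-out fall by b = 0.5, 1 or 2 per SD of attendance in the class arms.
- Drop-out is 20% in every arm, and random in TAU.

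**Simulation.** 5,000 per arm, three replicates averaged, random-intercept model by maximum likelihood without the random slope. Imputation was by regression on baseline, earlier visits and, in the class arms, attendance. True class-versus-TAU effect about 0.35.

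| Drop-outs lost before week 10 | g | b | Bias, HLM without attendance | Bias, attendance as auxiliary | Estimate, attendance as covariate (TAU = 0) |
|---|---|---|---|---|---|
| half | 0.15 | 1 | +0.013 | +0.003 | -0.106 |
| half | 0.30 | 1 | +0.030 | +0.001 | -0.563 |
| half | 0.30 | 2 | +0.038 | +0.003 | -0.543 |
| all | 0.15 | 1 | +0.019 | -0.001 | -0.098 |
| all | 0.30 | 1 | +0.050 | -0.006 | -0.564 |

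In single runs of 6,000 per arm with g = 0, the HLM matched the full-data effect within noise: 0.330 against 0.329, 0.346 against 0.347, and 0.344 against 0.345.

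**Check of the bias by formula.** If all drop-outs leave before week 10, only stayers contribute, so bias = g × E[A | stay], where A is standardised attendance. At 20% drop-out and b = 1, numerical integration gives E[A | stay] = 0.173. The bias is then 0.15 × 0.173 = 0.026 or 0.30 × 0.173 = 0.052, close to the simulated 0.019 and 0.050. Three consequences follow:

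- A negative g reverses the sign.
- If g, b and drop-out are equal in CBSST-Peer and SST-Peer, the two biases subtract to zero.
- The most extreme corner (b = 2, g = 0.30, everyone lost before week 10) gives 0.30 × 0.262 = 0.079, so 0.05 is not a ceiling.

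**Check of the covariate route.** With TAU coded as zero classes, the arm coefficient is the effect at zero attendance: 0.35 - 12 × g/4. For g = 0.15 this is 0.35 - 0.45 = -0.10; for g = 0.30 it is 0.35 - 0.90 = -0.55. Both agree with the table. If TAU were instead coded at the class-arm mean of 12, the same model would return about 0.35. The answer depends on a code for TAU that no data can supply.

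**Second calculation.** This used 60,000 class-arm subjects, 78-79% retention at week 32, 50-60% attenders, gains of 0.50-0.70 SD in attenders and 0-0.05 in others, all assumed. The average follow-up effect (true / maximum likelihood / maximum likelihood with attendance as auxiliary) was 0.303/0.335/0.303, 0.216/0.245/0.217 and 0.308/0.355/0.309. The overstatement is 0.032, 0.029 and 0.047 SD. The correction here was itself obtained by maximum likelihood. A further check at about 79% retention put the bias in the class-arm mean at about 0.005 to 0.03 SD.

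**The case against.** Likelihood-based mixed models under missing at random are a conventional primary analysis, and a stated preference does not forbid multiple imputation as a sensitivity analysis. Sensitivity analyses are commonly left to an analysis plan, which is not shown, so their absence is not the point. This stands. The point is what the article does fix: an unconditional ranking of methods, and a fit-selected covariate role for attendance.

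Four stronger readings are tempting, and the article does not support them.

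- **A reader might infer that preferring maximum likelihood is the error.** It is not. A joint likelihood can carry attendance as an auxiliary variable, and the second calculation did so. The limit lies in the single-outcome HLM described.
- **A reader might infer that the class arms will look better than they are.** That needs low attenders both to do worse and to miss more assessments. The article states neither. It is plausible if the classes work, but the driving inputs are assumed.
- **A reader might infer that missing classes by itself leads to withdrawal.** The rule also requires lost interest or no response. Assessments are attempted in everyone and transport is provided, so missed classes need not mean missed scores.
- **A reader might infer that TAU is free of similar loss.** The article does not say so. Disengagement in TAU could also predict missing and worse scores, which would shrink the bias in the contrast.

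The bias from omission is also small: 0.01 to 0.05 SD against a standard error near 0.10 is about 0.1 to 0.5 standard errors.

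**Conclusion.** The concern holds in a limited form. The outcome-covariate route for attendance conflicts with the intention-to-treat contrast against TAU, and the size of that problem depends on how TAU is coded and how strongly attendance predicts outcome.

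Leaving attendance out is the better primary choice. Under the assumed inputs it may overstate class arms versus TAU by about 0.01 to 0.05 SD, roughly 4% to 14% of d = 0.35 (0.013/0.35 to 0.050/0.35). The bias is zero if attendance does not predict outcome, smaller with less drop-out, and of opposite sign if low attenders do better. That CBSST-Peer versus SST-Peer is largely unaffected was reasoned from the formula, not simulated, and requires attendance to act alike in both arms.

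This justifies one pre-specified supportive analysis. It does not justify calling the maximum-likelihood primary analysis wrong, or resting the conclusion on two analyses with no rule for when they disagree.

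**What to change.** 1. Keep the HLM fitted by maximum likelihood, with its contrasts, as the primary analysis. Remove attendance from the candidate covariates of that model.
2. Delete the clause that ranks maximum likelihood above multiple imputation.
3. Pre-specify one supportive analysis with attendance as an auxiliary variable. Impute separately by arm from all ILSS visits, baseline BPRS and CAINS and, in the class arms only, the number of classes attended to date. Then fit the same HLM without attendance. An equivalent joint likelihood would also do.
4. Report it beside the primary result as a sensitivity check on the TAU contrasts, not as a second basis for the conclusion.

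The cost is plan wording and a few hours of programming, with no new data. The downside is one more analysis and possibly a slightly smaller estimated effect.
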